## **2. Study Design**

### **2.1 Study Overview**

The objective of this study was to assess the efficacy of acupuncture in the preventive treatment of MRM.

### **2.2 Background**

Migraine is a common neurological disorder. Population based studies suggest that 6% to 7% of men and 15% to 18% of women experience migraine (1, 2). More than 50% of female patients report that their migraines are associated with the menses(3). Attack onset is usually before the age of 20 years, with peak prevalence between the ages of 25 and 55 years, declining with menopause(4-6). Increasing evidence links menstrual migraine to the female sex hormones(3, 7).

Approximately 14% of female migraineurs have migraine only during menstruation (pure menstrual migraine (PMM)) while 60% suffer from migraine at both menses and other times during the menstrual cycle (menstrual-related migraine (MRM)) (8). Most of the data in the literature report that MRM causes significant limitations of daily activities (for example, nausea, vomiting, and photo-phonophobia), and the attacks are generally longer, more severe, and less drug-responsive than non-menstrual ones(9, 10).

Given the particular clinical picture that characterizes MRM, it is not surprising that the attacks are difficult to treat. The options available for the treatment of MRM include acute therapy and prophylaxis (short-term preventive therapy and long-term preventive therapy) (11-

13). Acute therapy is initiated first. As MRM is unique in its predictability, treatment can be targeted to the period of time when patients are most likely to experience migraine. The treatment window for menstrual migraine occurs between 2 days before and 3 days after the onset of menses(12). The goals of prophylactic strategies are to reduce attack frequency, severity and duration, improve responsiveness of treatment for acute attacks, improve function, and reduce disability. Prophylactic medications include non-steroidal anti-inflammatory drugs (NSAIDs), triptans, estrogen, magnesium, dihydroergotamine (DHE), methysergide, and vitamin E(13). Caution should be taken when the drug is used within the same month for treating migraine attacks occurring during perimenstrual period and outside perimenstrual period due to the risk of medication-overuse headache, a risk which is, however, common to all medications used for menstrual-migraine prophylaxis or treatment(13).

Acupuncture, which is one of the main treatment modalities of Traditional Chinese Medicine (TCM), has been used for both the prevention and treatment of diseases for over 2,000 years. Several studies (14-17) have already reported the encouraging results in the therapy for migraine by acupuncture. A German randomized controlled trial (n = 794) showed that 11 acupuncture treatments given within 6 weeks were at least as effective as a  $\beta$ -blocker taken daily over 6 months(14). Yang et al. found that acupuncture treatment was more effective and safer than topiramate (15). Wang and co-authors reported that acupuncture was more effective than flunarizine in decreasing the duration of migraine attacks(16). Therefore, acupuncture should be considered as an option for patients with migraine(17). Although the physiological mechanism is still unclear (18), in the last 40 years, many theoretically plausible models have been developed, such as the principle of counter-irritation diffuse noxious inhibitory control (DNIC) and the endorphin hypothesis Melzack's gate control theory (19-21). DNIC is regarded as a possible factor explaining central pain modulation through acupuncture (22). The endorphin hypothesis serves to explain a short-term analgesic effect of acupuncture, which is considered very robust.

However, based on a review of published literatures, the guidelines did not make treatment recommendation for acupuncture, because this therapy lacked adequate randomized controlled trials to support its effect. When reviewing the evidence of acupuncture for MRM, only one

published randomized controlled trial could be found(22). The objectives of that study were to introduce a new method for controlled trials of acupuncture for headache and to examine the role of needling per se. No significant differences were found between the verum group and the placebo group.

In this study, we will perform a randomized controlled trial to investigate the efficacy of acupuncture treatment as prophylaxis for MRM.

## **2.3 Study Objectives and Hypothesis**

The objective of this study is to assess the efficacy of acupuncture as the preventive treatment for women with MRM.

We hypothesize that acupuncture is different from medication in decreasing migraine days for women with MRM.

## **2.4 Methodology**

### **2.4.1 Trial design**

This is a multicenter, double-dummy, participant-blinded, randomized controlled clinical trial at 4 centers in China.

#### **2.4.1.1 Randomization**

This study, we will use blocks randomization, stratified according to center. A central randomization system will be applied in our trial. The randomizing scheme will be produced by staff of the Research Center of Clinical Epidemiology affiliated to Peking University using statistical analysis software SAS9.4 with “proc plan” program. After production, it will be signed and sealed by the staff who produce it and keep by other staff who take no part in this trial. It will not be allowed to be checked by anyone except the top system administrator. Acupuncturists in each center will be responsible for getting random numbers. Via inputting the participants’ sex and birthday in the central randomization system through the phone or the web, they will get the random number.

#### **2.4.1.2 Blinding**

In this study, participants, outcome assessors and statisticians will be blinded to treatment allocation. To ensure all participants being blinded to their group allocation, the placebo naproxen will be prepared by Diao Group Chengdu Pharmaceutical LTD (Chengdu, China) with identical taste, smell and appearance as true naproxen, and the sham acupuncture will produce same stimulation as true acupuncture. Participants of different groups will be treated separately and blinded to which acupuncture method they would receive. For blinding assessment, all participants will be requested to guess whether they received ‘True acupuncture plus placebo naproxen’ or ‘Sham acupuncture plus naproxen’ within five minutes after their treatments at cycles 1.5 and 3.

#### **2.4.1.3 Sample Size**

According to the previous pilot study(23), we anticipated that the number of migraine days over 12 weeks would be 3.1(SD 2.7) days in the acupuncture group and 5.2 (SD 4.4) in the medication group. With a 2-sided significance level of 5% and power of 90%, 68 participants for each group would be required, as calculated by PASS 2008 software (NCSS, Kaysville, Utah, USA). With an estimated loss-to-follow-up rate of 20%, we planned to enroll a total of 172 participants with 86 participants per group.

#### **2.4.2 Subjects**

##### **2.4.2.1 Eligibility criteria**

Women will be included in the study if they met the following criteria. (1) Diagnosis of MRM(24): MRM without aura (code A1.1.2), in which migraine without aura always occurs on days  $1 \pm 2$  of menstruation in at least two out of three menstrual cycles, and at other times due to different triggering factors or for no apparent specific reason (International Classification of Headache Disorders - second edition [ICHD-II]); (2) Regular menstrual cycle (25-35 days); (3) could predict within three days both the onset of menstruation and perimenstrual migraine attacks; (4) Repeated migraine attacks, frequency of nonmenstrual migraine is more than once

a month; (5) Written informed consent.

#### **2.4.2.2 Exclusion criteria**

Women will be excluded from the study if they met the following criteria. (1) Chronic migraine, tension-type headache, cluster headache, and other primary headaches; (2) Secondary headache and other neurological diseases; (3) Relatively severe systemic diseases (cardiovascular disease, acute infectious disease, hematopathy, endocrinopathy, and allergy); (4) Headache caused by otorhinolaryngology diseases or intracranial pathological changes; (5) Oral contraceptives, pregnancy, or lactation period; (6) Use of prophylactic migraine medication in the last 3 months; (7) Participation in another clinical trial.

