#### **2.4.2.3 Subject Withdrawals**

There will be at least one on-call clinician in each center. They would assess the severe adverse events (SAEs) and then determine whether the participant to continue or terminate the trial. Subjects may leave the study at their own discretion or the investigator may determine whether it is in the best interest of subjects to withdraw from the trial due to worsening of symptoms, or the occurrence of a serious adverse event.

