#### **2.4.2.4 Subject Recruitment, Screening and Group Assignment**

Two strategies will be used to recruit participants with MRM. One is to recruit participants in outpatient clinics from the four centers mentioned above. The other is to show recruitment posters outside the clinics. Research assistants of each center will preliminarily screen the participants by recording their disease condition, history of the disease and treatment, and the demographic data. Experienced neurologist in each trial center will take charge of the diagnosis of MRM. Potential participants will receive a 3-cycle baseline assessment, during which they have to fill out headache diaries. Eligible participants then will be randomized to acupuncture or medication group. Acupuncturists will be in charge of participant assignment, and the trial procedures. Acupuncturists and neurologists will be responsible for the assessment of safety during treatment, including the acupuncture-related

AEs or medication-related adverse events (AEs). During the trial, independent evaluators of each center will instruct the participants how to fill in their headache diaries. The evaluators will record the data on the case report form (CRF) through the whole trial period. The subject flow was shown in **Figure 1**.

[figure not shown]

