**Figure 2. Trial flow chart**

|                                        | STUDY PERIOD |            |           |         |       |           |    |    |
|----------------------------------------|--------------|------------|-----------|---------|-------|-----------|----|----|
|                                        | Baseline     | Allocation | Treatment |         |       | Follow-up |    |    |
| VISIT                                  | 1            | 0          | 2         | 3       | 4     | 5         | 6  | 7  |
| TIMEPOINT(C, cycle)                    | -3-0C        |            | 1C        | 2C      | 3C    | 4C        | 5C | 6C |
| Enrollment                      |              |            |           |         |       |           |    |    |
| Screening                              | ×            |            |           |         |       |           |    |    |
| Informed consent                       | ×            |            |           |         |       |           |    |    |
| Eligibility criteria                   | ×            |            |           |         |       |           |    |    |
| Demography
Characteristics          | ×            |            |           |         |       |           |    |    |
| Disease history of MRM                 | ×            |            |           |         |       |           |    |    |
| Laboratory test                        | ×            |            |           |         | ×     |           |    |    |
| Randomization                          |              | ×          |           |         |       |           |    |    |
| Interventions                   |              |            |           |         |       |           |    |    |
| True acupuncture plus placebo naproxen |              |            | ×         | ×       | ×     |           |    |    |
| Sham acupuncture plus true naproxen    |              |            | ×         | ×       | ×     |           |    |    |
| Assessments                     |              |            |           |         |       |           |    |    |
| Headache diary                         | ×            |            | ×         | ×       | ×     | ×         | ×  | ×  |
| Migraine days                          | ×            |            | ×         | ×       | ×     | ×         | ×  | ×  |
| Migraine hours                         | ×            |            | ×         | ×       | ×     | ×         | ×  | ×  |

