**Figure 3. The schedule of enrollment, interventions, and assessments**

## **2.4.4 Outcomes Measurements**

### **2.4.4.1 Primary Outcome**

The primary outcome will be the change from baseline in average number of migraine days per perimenstrual period over cycles 1-3, assessed using headache diary data(14).

Calculation methods:

Average number of migraine days per perimenstrual period over cycles 1-3 is calculated as the cycle average, equals the total of migraine days during perimenstrual period over cycle 1, cycle 2 and cycle 3 divided by 3.

The frequency and severity of migraine will be based on data from headache diary recorded by participants on baseline (Cycle- -3 to Cycle-0), treatment phase (Cycle-1 to Cycle-3) and follow-up phase (Cycle-4 to Cycle-6). In the diaries, the participants recorded on diary cards with details of their migraine attacks, including the time of headache attack and cease, intensity, frequency, location (the forehead, top, temporal, and back of the head), cause of the headache, concomitant symptoms, and acute pain medications (if any) for each migraine attack. Additionally, participants were required to record information of their menstruation and the dates of receiving acupuncture treatments in their headache diaries. If acute pain medications were taken, participants were required to document the name, dosage, and time of taking the medicine, time of pain relief, and side effects of acute pain medication. In each center, data of headache diaries will be checked by two full-time research assistants first, and then entered into e-headache diary database by two independent data entry clerks. The audited data of e-headache diary will be finally carried forward into effectiveness data by statisticians.

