### **3. Safety Assessment**

All the serious adverse events (SAEs) and adverse events (AEs) will be recorded and measured by both participants themselves and clinicians including neurologists and acupuncturists through the whole trial. In our trial, the SAEs will be defined as events requiring hospitalization, causing disability or impaired ability to work, threatening life or resulting in death. AEs will be categorized as acupuncture related or medication related based on its potential association with acupuncture needling procedure by acupuncturists or medication intake procedure within 24 hours. The acupuncture related AEs defined as follows: broken needle, needle phobia, intense pricking, pricking lasting more than half an hour (no matter how intense it is) after acupuncture, hematoma, dermorrhagia, infection, abscess formation at the needling site, other discomfort induced by acupuncture (such as lassitude, numbness, somnolence, nausea, vomiting, palpitation, dizziness, headache, loss of appetite, insomnia, etc), and aggravation of existing symptoms, etc. Given that acupuncture is a minimally invasive therapy inevitably causing pain, pricking with a spontaneously remission within 30 min after acupuncture will be not regarded as acupuncture related AE. The medication related AEs defined as follows: nausea, palpitations, dyspepsia, upper abdominal pain, heartburn, somnolence, dizziness, and sweating attack, etc. The numbers of participants and events of AEs will be recorded. We will compare the proportion of participants who get treatment-emergent adverse events (TEAEs). Participants who get TEAEs at least once will be counted in for the comparison of the proportion.

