#### **4.2 Treatment of medication group**

In the medication group, participants will be given naproxen sustained release tablets (Diao Group Chengdu Pharmaceutical LTD, Chengdu, China) plus sham acupuncture. Naproxen sustained release tablets will be taken with a peri-menstrual dosing strategy (250mg/tablet, 2 tablets each time, once per day), which will start three days before each predicted onset of the menstruation and continue until the end of their menstrual cycle for 3 cycles. In the event that menstruation begins later than predicted, no adjustment to the treatment will be made. If the MRM occurs earlier than predicted, participants will be asked to begin taking naproxen immediately and one day earlier in the next cycle in an attempt to provide prophylactic coverage. The timing of treatment will be based on information collected (a headache diary) during the baseline phase and will not account for variability in menstruation and migraine onset during the treatment phase.

The method of applying blunt needles on effective acupuncture points will be not used in this trial as control for following reason: patients in China are very familiar with the sensations caused by acupuncture and therefore they may easily identify the blunt needles.

To make the needling stimulation consistent, the same type, size, and number of needles will be used for both groups. In order to avoid possible therapeutic effects of sham acupuncture,

the non-effective acupoints are chosen by the following three rules: (1) Acupuncture points that are defined as unrelated to headache or menstruation based on a vast amount of Chinese medicine reference books (26 ancient Chinese books of acupuncture, three Chinese acupuncture textbooks and >100 acupuncture research literatures); (2) 15 acupuncture points in the vicinity of elbow and knee joints are selected while the acupuncture points on the head, hands, feet, and trunk are excluded; (3) To mimic the nature of selecting points based on syndrome differentiation, the 15 sham points in the vicinity of elbow and knee joints are further randomly assigned to 3 subgroups: B, C, D. Each subgroup will have two points on the arms and three points on the legs. The participants in the medication group will be further randomly assigned into one of these three subgroups via central randomization system. Participants will be treated individually to avoid communication on the treatments they received.

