### **7.4 Medical Coding**

A data administrator who has the medicine background will take charge of the medical coding. The contents of the coding are the clinical history, adverse events, and combined medication. The clinical history and adverse events will be coded through MedDRA dictionary (Version 13.0), and the combined medication will be coded via WHO DD dictionary (Version 2007.03). The lead researchers will verify the coded e-files.

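### The exclusion lists do not bar women with a past peptic ulcer or GI bleed, or with non-allergic NSAID intolerance, from being randomised to naproxen, and have no general contraindication clause

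*Supplement*

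**What the plan says.** The protocol (2.4.2.2) and the SAP (3.2.2) carry the same seven exclusions. The one on general health is "Relatively severe systemic diseases (cardiovascular disease, acute infectious disease, hematopathy, endocrinopathy, and allergy", where the bracket closes. Exclusion 5 adds oral contraceptive use, pregnancy and lactation. The other five concern headache type and cause, recent migraine prophylaxis and other trials. The inclusion criteria (protocol 2.4.2.1, SAP 3.2.1) say nothing about tolerance of the study drug.

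Protocol 4.2 gives the medication group sustained-release naproxen on a "peri-menstrual dosing strategy (250mg/tablet, 2 tablets each time, once per day), which will start three days before each predicted onset" of menses, carried on to the end of the menstrual cycle, for three cycles. Section 3 foresees upper-gastrointestinal effects: "The medication related AEs defined as follows: nausea, palpitations, dyspepsia, upper abdominal pain, heartburn", among others.

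Before randomisation, section 2.4.2.4 has research assistants record each woman's condition, the history of the disease and its treatment, and demographic data. The neurologist makes the migraine diagnosis. After entry, "Acupuncturists and neurologists will be responsible for the assessment of safety during treatment", and on-call clinicians deal with severe events: "They would assess the severe adverse events (SAEs) and then determine whether the participant to continue or terminate the trial" (2.4.2.3).

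**The concern.** A plan that randomises to an NSAID would normally screen out women whose history makes the drug a poor choice for them. Here a woman with a healed ulcer, a previous gastrointestinal bleed, or known trouble with NSAIDs short of allergy meets every written criterion and can be allocated to repeated naproxen courses. Because she is blinded, she cannot tell whether her tablets are active.

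What is at stake is the safety of those women. That such histories raise the risk of naproxen is a general clinical assumption. The documents support it only indirectly, by listing dyspepsia, upper abdominal pain and heartburn as medication-related events.

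**Working it through.** **Step 1. Compare the lists with histories that bear on naproxen.**

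| History | Covered by either list? |
|---|---|
| Relatively severe cardiovascular disease | Yes, exclusion 3 |
| Blood disorder, including a bleeding disorder | Yes, exclusion 3, if relatively severe |
| Allergy, including to naproxen | Yes on a reasonable reading of exclusion 3 |
| Pregnancy, lactation | Yes, exclusion 5 |
| Active severe ulcer | Possibly, if the bracket in exclusion 3 gives examples |
| Healed ulcer or past gastrointestinal bleed | No: not a current severe systemic disease on either reading |
| Non-allergic intolerance to naproxen or another NSAID | No |
| Any other contraindication to the study drug | No general clause |

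**Step 2. Look for another barrier before randomisation.**
- Section 2.4.2.4 collects history at screening but attaches no exclusion to it.
- The only history row in the schedule (protocol Figure 3, SAP section 4) is "Disease history of MRM".
- Section 7.4 suggests that a wider history is held: "The contents of the coding are the clinical history, adverse events, and combined medication". It does not say what that history contains or when it is taken.
- The headache diary, kept for three baseline cycles, can show drug side effects, but conditionally: "If acute pain medications were taken, participants were required to document" them (2.4.4.1).
- A laboratory test is scheduled at baseline, with no content or threshold given.
- Under 2.4.1.1 the acupuncturist obtains the random number by entering sex and birthday. No step there confirms that naproxen is suitable.

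**Step 3. Safeguards after entry.** The safety assessment, on-call review and withdrawal rules all act once the woman is in the trial.

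**Step 4. Size of the exposure.**
- Daily dose: 2 × 250 mg = 500 mg (protocol 4.2).
- Menses length is not given; assume 3 to 7 days. If menses start on the predicted day and dosing stops when they end, a course is 3 + 3 = 6 to 3 + 7 = 10 days.
- Three cycles: 3 × 6 = 18 to 3 × 10 = 30 days, or 18 × 0.5 g = 9 g to 30 × 0.5 g = 15 g.
- Late menses, or an early attack that brings dosing forward, lengthens a course; early menses shortens it.
- Read literally, the stopping rule runs to the end of the cycle. With cycles of 25 to 35 days (inclusion 2), dosing would be continuous: 3 + 3 × 25 = 78 to 3 + 3 × 35 = 108 days. The peri-menstrual label makes the shorter reading more likely, but the text does not settle it.

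**Step 5. Number of women.** The share with such a history is not in the documents, so only a rate can be given. For each 1%, 0.01 × 86 = 0.86 women would be assigned naproxen, and 0.01 × 172 = 1.72 would not be enrolled under the added criterion.

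**The case against.** The strongest reply is that the plan is not silent on naproxen safety. It excludes relatively severe cardiovascular disease, blood disorders, allergy, pregnancy and lactation. The words 'relatively severe' have no threshold, so someone must exercise judgement, and that judgement could reach an active severe ulcer. Staff take a disease and treatment history, section 4.3 has treatments already used recorded, clinical history is coded separately from adverse events, and the baseline diary may reveal a bad reaction to an NSAID. Courses are probably short and intermittent, with clinicians on call. The consent text and the flow figures are not shown, so what women were told or asked cannot be checked. The section 3 list names symptoms, not ulceration or bleeding.

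Much of this stands, and it rules out stronger readings that a reader might infer:
- **That nothing relevant to naproxen is excluded.** Several such conditions are. What is missing is the two histories and a general clause.
- **That eligibility leaves no room for judgement.** Exclusion 3 does, but for current systemic disease, not for a resolved ulcer or simple intolerance.
- **That screening asks only about migraine.** The documents do not show this. They show that no rule acts on the answers.
- **That exposure is a known number of days.** It depends on an assumed menses length and on how the stopping rule is read.

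None of the listed records is an exclusion criterion, and neither is a warning in a consent form. Both eligibility lists are shown in full, so the gap in them does not depend on the withheld pages.

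**Conclusion.** The point holds in this limited form. As written, the plan allows a woman with a past peptic ulcer or gastrointestinal bleed, or with non-allergic NSAID intolerance, to be randomised to naproxen 500 mg daily. The likely exposure is about 18 to 30 days in total, or 9 to 15 g, assuming menses of 3 to 7 days that start as predicted and dosing that stops when they end. The literal stopping rule would give more.

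The conclusion rests on the text of the lists and on the general clinical premise that these histories raise the risk of naproxen. How many women are affected is unknown, and nothing shows that any were enrolled. A reader might also infer a bias or a loss of power. The documents give no support for that: the gap applies equally to all women before allocation, and no sample-size or analysis figure depends on it. It is a worthwhile and cheap safety improvement, not a flaw in the comparison.

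**What to change.** Add one exclusion to protocol 2.4.2.2 and mirror it in SAP 3.2.2 so that the lists still agree: *history of peptic ulcer or gastrointestinal bleeding; known intolerance or hypersensitivity to naproxen or any other NSAID; or any other contraindication to the study naproxen.* Apply it to every woman, whichever group she might enter, before a random number is requested.

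Add a short history question on these points at visit 1. Baseline diary entries on side effects can support the answer but should not replace it, because they exist only for women who took acute medication.

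The cost is one criterion in two places, one screening question, and about 1.7 of 172 women not enrolled for each 1% with such a history. Further recruitment would replace them. Randomisation, blinding and the analysis are unchanged.
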